### Exclusion criteria

Age < 2 years or > 18 years.Nephritis not caused by HSP.Persistent hypertension, renal insufficiency, or azotemia.If undergoing kidney biopsy, a renal pathological grade above IV (including IV) according to ISKDC guidelines with a ratio of crescents, loop necrosis, and adhesion of glomerular and renal capsules higher than 20%.Allergic to the treatment medicine.Other clinical classifications, such as NS, RPGN, and ARI.

### Intervention

The participants will be divided into two groups: an experimental group treated with TCM and a control group receiving regular treatment. In each arm, light type and heavy type HSPN will be reclassified based on the level of proteinuria and biopsy results. Eligible patients will be treated and observed for a total of 48 weeks. The first 12 weeks comprise the drug therapy stage, and the next 36 weeks comprise a follow-up observation stage.
Treatment stage (0–12 weeks).
TCM group.

TG: for light type HSPN, the initial dosage is 1.5 mg/kg/day (maximum of 90 mg) for the first 4 weeks. For heavy type HSPN, the initial dosage is 2 mg/kg/day for the first 2 weeks and is reduced to 1.5 mg/kg/day (maximum of 90 mg) for the following 2 weeks. Both groups will continue to receive treatment for another 8 weeks at a dosage of 1 mg/kg/day taken orally 2–3 times per day for a total of 12 weeks.

Tanshinone IIa sodium sulfonate injection (TIIa): an intravenous drip of TIIa administered at a dosage of 1 mg/kg/day (maximum of 50 mg) in combination with 100–250 ml of a 5% glucose solution (GS) for 2 weeks.

TCM based on syndrome differentiation: in TCM-treated patients, Chinese herbs will be administered as Qingrezhixue granules according to syndrome differentiation for 12 weeks. The specific TCM treatments are presented in Table 2.
b)Regular group.
GC: for severe type HSPN, prednisone will be given orally at 1.0 mg/kg/day for 12 weeks. In the first 4 weeks, GC is given at 1.0 mg/kg/day (maximum dose should not exceed 30 mg). The initial dose (1.0 mg/kg/day) should be reduced by 5 mg every other day for 4–8 weeks, and the dose should be reduced by 5–10 mg every week for 8–12 weeks. GC is not necessary and will not be administered for light type HSPN.LMWHC injection: both types will be given LMWHC via a subcutaneous injection at 100u/kg/d once a day for the first 2 weeks.Benazepril hydrochloride tablets (Lotensin): both types will be given Lotensin at 5–10 mg/day orally once per day for 12 weeks.Dipyridamole tablets (Persantine): both types will be given Persantine at 3 mg/kg orally three times per day for 12 weeks.Chinese medicine placebo: to increase compliance by patients seeking TCM treatment in Chinese hospitals, one kind of granule placebo similar to Qingrezhixue granules will be used in the control group, and there is no additional placebo used to blind for the other components of the TCM intervention (TG tablets and tanshinone IIa injections).Changes in proteinuria and hematuria and liver and kidney function will be monitored during treatment, as shown in Table 3.

**Table 2 Tab2:** Herb addition based on traditional Chinese medicine syndrome differentiation

Yin deficiency complicated with blood stasis Add Chinese herbs as Qingrezhixue granules: *Rhizoma anemarrhenae*, *Cortex phellodendri*, *Rhizoma polygonati*	
Main symptoms of yin deficiency	Red tongue with less or no moss and a dark red throat, a low-grade fever with night sweat, sparse purpura
Secondary symptoms of yin deficiency	Feverishness in the palms and soles, dry mouth with thirst, a weak and rapid pulse
Symptoms of blood stasis	Dark purple tongue or bruises on tongue body; varicose veins or blood stasis in sublingual veins; fixed pain or intense pain causing an aversion to touch; thrombogenesis; dark or blue color (cyanosis) in the face, mouth, or gums, around the eyes, or in the lips and extremities; sluggish or intermittent pulse; hematuresis, epistaxis, ecchymosis, or tarry stool; dark and dull complexion; laboratory examination indicating blood circulation stasis
Diagnostic criteria	2 main symptoms of yin deficiency (or 1 main + 2 secondary symptoms) + 1 main symptom of blood stasis
Blood heat complicated with blood stasis Add Chinese herbs as Qingrezhixue granules: ComuBuball, Radix arnebiae seu lithospermi	
Main symptoms of blood heat	Excessive skin petechiae or bright red bruises located close to each other, anxiety, dry mouth, and thirst
Secondary symptoms of blood heat	Red tongue with yellow moss, strong and rapid pulse, constipation
Symptoms of blood stasis	Red tongue with yellow moss, strong and rapid pulse, constipation
Diagnostic criteria	2 main symptoms of blood heat (or 1 main symptom + 2 secondary symptoms) + 1 main symptom of blood stasis
Wind heat complicated with blood stasis Add Chinese herbs as Qingrezhixue granules: *Lonicera japonica*, Fructus Forsythiae, radix platycodonis, mint, bamboo leaf, *Schizonepetae*, Burdocks	
Main symptoms of wind heat	Bright red throat, fever, yellow mucus, small or itchy rash
Secondary symptoms of wind heat	Red tongue with thin yellow or white moss, light and rapid pulse, aversion to wind, cough
Symptoms of blood stasis	Red tongue with thin yellow or white moss, light and rapid pulse, aversion to wind, cough
Diagnostic criteria	2 main symptoms of wind heat (or 1 main symptom + 2 secondary symptoms) + 1 main symptom of blood stasis
Both qi and yin deficiency complicated with blood stasis Add Chinese herbs as Qingrezhixue granules: Astragalus, Radix pseudostellariae, Glossy Privet Fruit, *Eclipta alba*, Rhizoma polygonati	
Main symptoms of qi deficiency	Weak and easily tired, bad appetite or thin stool, susceptible to cold or diarrhea
Secondary symptoms of qi deficiency	Pale complexion, pale tongue with thin moss or thin and fat tongue with teeth marks, thin and weak pulse
Symptoms of yin deficiency/blood stasis	Pale complexion, pale tongue with thin moss or thin and fat tongue with teeth marks, thin and weak pulse
Diagnostic criteria	2 main symptoms of qi deficiency (or 1 main symptom + 2 secondary symptoms) + 2 main symptoms of yin deficiency (or 1 main symptom + 2 secondary symptoms) + 1 main symptom of blood stasis
Dampness heat complicated with blood stasis Add Chinese herbs as Qingrezhixue granules: *Scutellaria baicalensis*, Cogongrass rhizome, Herba pyrrosiae	
Main symptoms of dampness heat	Yellow complexion, dark urine or sticky stool, yellow greasy coating on the tongue
Secondary symptoms of dampness heat	Skin sores (e.g., furuncles), bitter taste and bad smell in the mouth, rapid and weak pulse
Symptoms of blood stasis	Skin sores (e.g., furuncles), bitter taste and bad smell in the mouth, rapid and weak pulse
Diagnostic criteria	2 main symptoms of blood heat (or 1 main symptom + 2 secondary symptoms) + 1 main symptom of blood stasis

**Table 3 Tab3:** Observation protocol to be followed during treatment and follow-up

Observed indicator/week		Treatment stage (week)								Follow-up stage (week)								
		0	1	2	4	6	8	10	12	16	20	24	28	32	36	40	44	48
Main	24-h urinary protein quantity	×	×	×	×	×	×	×	×	×	×	×	×	×	×	×	×	×
Secondary	Urine red blood cells	×	×	×	×	×	×	×	×	×	×	×	×	×	×	×	×	×
Security	Routine blood tests	×	×	×	×	×	×	×	×	×	×	×	×	×	×	×	×	×
	Hepatic and renal function	×	×	×	×		×		×		×		×		×		×	×

2.Follow-up stage (12–48 weeks).

The 12-week treatment stage will be followed by a 36-week follow-up stage. The main aim of the follow-up is to monitor a series of laboratory indicators and determine the disease recurrence rate. The details are presented in Table 2.

In patients who meet the clinical control standards after 12 weeks of treatment, medication will be stopped and the patients will begin follow-up. The clinical control standards mean that RBC counts and 24-h protein in urine are at normal levels, and urine routine examinations are negative for protein and occult blood. For those patients who do not meet the clinical control standards by 12 weeks, other treatment options could be appropriately selected in the professional judgment of the clinicians. The clinicians who are evaluating the follow-up laboratory results (and determining whether there is a relapse or whether the patient has reached clinical control standards) are not blinded to the patient’s treatment assignment. The criteria for efficacy evaluation are presented in Table 4.

**Table 4 Tab4:** Criteria for efficacy evaluation

Primary outcome	Clinical control rate	Significant efficiency	Effective rate	Ineffective rate
PRO in urine	Negative	PRO decreased by 2+	PRO decreased by +	PRO decreased less than +
	24-h urinary protein quantity is normal	24-h urinary protein quantity reduced > 50%	24-h urinary protein quantity reduced between 30 and 50%	24-h urinary protein quantity reduced < 30% or no change
RBC in urine	U-OB: negative	U-OB: RBC reduction ≥ ++/HP	U-OB: RBC reduction ≥ +/HP	U-OB: no improvement or aggravation in RBC
	RBC ≤ 5/HP	RBC count decreased By > 50%	RBC count decreased between 30 and 50%	RBC count decreased < 30% or no change
Total therapeutic effect	Meet all these requirements	Meet all these requirements	Meet all these requirements	Meet all these requirements

*RBC* red blood cells, *U-OB* urine occult blood, *PRO* Urinary protein, *HP* high power microscope

If the disease relapses during follow-up, the details of the recurrence will be recorded and the appropriate treatment administered in a timely manner while follow-up is completed. Other treatment options are available to patients who do not meet the clinical control standards, and it will be necessary to record any decisions and proceed with the follow-up stage.

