### Outcomes

The study will be conducted over a period of 1 year (48 weeks) and will include a treatment period of 3 months (12 weeks) and an observation period of 9 months (36 weeks). In all, one primary outcome indicator, one secondary outcome indicator, and four security indexes will be analyzed:
Primary outcome indicator: 24-h urinary protein quantity.

Any change in total urine protein level at 24 h will be assumed to directly reflect a therapeutic effect; hence, this clinical laboratory index should be recorded every 2 weeks during the treatment period and every 4 weeks during the follow-up period (17 times in total). In addition, creatinine excretion measured vs expected for gender will be detected at the same time to verify the adequacy of 24-h urine collection indirectly.

Total urine protein at 24 h is the most important outcome. In previous studies, we found that the improvement of urinary protein of TG at week 4 and week 8 was better than that of the control group, while the difference at week 12 was not significant. Based on these subtypes, this study will further explore the difference in treatment between the two groups. Therefore, we will set 17 nodes, including the treatment period and the follow-up period, to compare the differences in urine protein between the two groups at each node, rather than only retaining the last result at 48 weeks.
2)Secondary outcome indicator: red blood cells in urine.

Compared to the primary indicator, the urine red blood cell count is considered secondary because urine red blood cells recede more slowly than protein recedes. This clinical laboratory index should be recorded at the same points during treatment and follow-up as the primary outcome indicator (17 times in total).
3)Security indexes.

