### Statistical analysis

All statistical analyses in the study will be carried out by a third party, the Chinese Academy of Traditional Chinese Medicine, using SAS version 6.12, which is validated software for clinical studies. Logistic regression is used to show a difference in the prevalence of clinical control/remission in both groups, including age, gender, place of residence, parents’ educational background, and so on. For the outcome “time from positive to negative for urinary protein and urinary occult blood”, a Cox proportional hazards model is used. The incidence is described for adverse events and Fisher’s test will be used for comparison. Besides, groups and time of therapy on curative effect will be considered. If there are interaction effects between groups, simple effect analysis is performed; if not, grouping effect/time of therapy on curative effect should be considered separately.

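### Nine of the 17 primary protein nodes fall after the 12-week programmes and mix in clinician-chosen treatment; control and relapse are called by clinicians who know the arm, and relapse has no stated criterion.

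*Protocol article*

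**What the plan says.** Intervention sets the time frame: "The first 12 weeks comprise the drug therapy stage, and the next 36 weeks comprise a follow-up observation stage". Outcomes makes 24-h urinary protein the single primary indicator and plans between-group comparisons throughout: "we will set 17 nodes, including the treatment period and the follow-up period, to compare the differences in urine protein". The same section assumes that a change in this value reflects the effect of treatment directly.

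Intervention, follow-up stage, gives the rules after week 12. Children who meet the clinical control standards stop medication. For the others, "other treatment options could be appropriately selected in the professional judgment of the clinicians". Children who relapse receive treatment that is not specified further. In both cases the decision or event is recorded and follow-up continues.

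Part of the purpose of follow-up is to "determine the disease recurrence rate". The section also discloses that "The clinicians who are evaluating the follow-up laboratory results", and who decide on relapse and control, know the arm. Control is defined by laboratory results: red cells and 24-h protein normal, dipstick protein and occult blood negative. The article gives no corresponding definition of relapse.

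Under Statistical analysis, "All statistical analyses in the study will be carried out by a third party".

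**The concern.** The study is meant to evaluate two 12-week programmes. After week 12, a fall in protein may come from the programme, from treatment added later, or from both. The added treatment is chosen by clinicians who know the arm, and it goes to the children who did worse. Reading those nodes as the programmes' own effect, as the assumption in Outcomes invites, would credit or blame a programme for drugs outside it.

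Recurrence raises a second problem. Only a child who reached control can relapse. A recurrence rate among such children compares groups formed by response after randomisation, so the arms need no longer be alike. Relapse is also an unblinded call without a stated criterion, so knowledge of the arm can enter it.

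**Working it through.** **1. Reproduce the 17 nodes.** Outcomes gives the frequency as "every 2 weeks during the treatment period and every 4 weeks during the follow-up period (17 times in total". Table 3 lists:
- treatment stage: weeks 0, 1, 2, 4, 6, 8, 10, 12 = 8 nodes
- follow-up stage: weeks 16, 20, 24, 28, 32, 36, 40, 44, 48 = 9 nodes

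8 + 9 = 17, as stated. (A strict two-week interval from 0 to 12 gives only 7; the week 1 visit in Table 3 makes up the total.) Week 0 is baseline, so 9 of the 16 post-baseline nodes, or 56%, fall after the programmes.

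**2. How many children are open to added treatment.** The week-12 control rate is not given, so this is an assumption. With 500 children at 2:1 (333 and 167):
- If week 12 equalled the week-4 rates in Sample size calculation (48.6% and 35.7%): 333 × 0.514 = 171 and 167 × 0.643 = 107, together 278 of 500 = 56%.
- At 70%, 80% or 90% control in both arms: 30%, 20% or 10%.

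Relapsing children add to these figures.

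**3. What added treatment can do to a difference.** Let p be the control rate at week 12 and r the share of uncontrolled children whom later treatment brings into control. Then

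gap = [pT + (1 − pT) rT] − [pC + (1 − pC) rC].

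As an illustration only, take pT = 48.6% and pC = 35.7%, a gap of 12.9 points. Power is two-sided at 0.05 with 333 and 167 children.

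| rT | rC | TCM | Control | Gap (points) | Power |
|---|---|---|---|---|---|
| 0 | 0 | 48.6% | 35.7% | 12.9 | 79% |
| 25% | 25% | 61.5% | 51.8% | 9.7 | 54% |
| 50% | 50% | 74.3% | 67.8% | 6.5 | 33% |
| 75% | 75% | 87.1% | 83.9% | 3.2 | 17% |
| 25% | 50% | 61.5% | 67.8% | -6.4 | |
| 50% | 25% | 74.3% | 51.8% | +22.5 | |

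These inputs are week-4 rates of proteinuria control. Outcomes reports that the earlier difference was not significant at week 12, so a gap of 12.9 points there is not what the article leads one to expect. With no gap at week 12 (70% in both arms), rT = 25% and rC = 50% give 77.5% − 85.0% = -7.5 points, and swapping the rates gives +7.5. A difference can therefore also be created by later care alone.

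**4. The passages on further drugs.** The follow-up text leaves the choice after week 12 to the clinician and keeps the child in follow-up. The section on abscission or termination counts use of non-permitted drugs as a reason for abscission, naming hormones and immunosuppressants that the trial does not mention. The article does not say whether that restriction applies after week 12. As worded, it does not exclude the other arm's drugs.

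**The case against.** The strongest reply is that nothing here breaks randomisation at the later nodes. Decisions are recorded, follow-up continues, and intention-to-treat analysis is foreseen. If all children are followed and analysed as randomised, weeks 16 to 48 give a valid comparison of starting programme plus later care. This stands. A reader might infer that the later nodes do not compare the randomised groups at all; the documents do not support that. The condition does matter, however: the termination rules let children with serious adverse events or no effect after 4 weeks leave both follow-up and analysis, which weakens the treatment-policy reading.

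Other parts of the reply also stand:
- Treatment is not free for everyone after week 12; children in control stop medication by rule.
- 24-h protein is a laboratory quantity. Knowledge of the arm reaches it through the choice of treatment, not through the reading. The judgement problem concerns control and relapse.
- Recurrence is not among the outcomes listed under Outcomes, and no denominator or between-arm test is stated. The comparison among responders is a risk to close off, not a stated analysis.
- The handling of values after added treatment is commonly left to an analysis plan, which is not shown. What the article itself fixes is the list of 17 primary nodes and the assumption about what a protein change means.

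Making sustained control without added treatment the main follow-up outcome may be tempting. It would place the unblinded decision to treat inside the outcome, and with data collection over it would look like an endpoint chosen late. Nor does recurrence over all randomised children cure the selection: an arm in which nobody reached control would show no recurrence.

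**Conclusion.** The point holds in limited form. Nine of 17 primary nodes measure the 12-week programme together with later discretionary care, so they cannot isolate the programmes, and the assumption in Outcomes fails there. The count is exact. The effect on the results is unknown: a reader might infer that true differences must shrink or reverse, but they may also widen or arise from nothing, depending on week-12 control rates and the success of later treatment, neither of which the article gives. The figures in the table show a mechanism and are not forecasts.

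Separately, control and relapse are judged with knowledge of the arm. For control this is avoidable, because the criteria are laboratory values. For relapse it matters more, because no criterion is stated. Any between-arm recurrence rate among responders would compare subsets selected after randomisation.

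**What to change.** 1. The third-party statistician derives control and relapse by program from recorded laboratory values, with arm masked and one analysis cut-off per test across centres (Quality control attaches each centre's own reference values). The sponsor fixes the laboratory definition of relapse in a dated document before arm codes are opened. Clinicians' calls are used for care only. Table 3 has no dipstick row, so first check that dipstick results were captured at every node.
2. Conclusions about the 12-week programmes rest on nodes up to week 12. Weeks 16 to 48 are reported in all randomised children as a treatment-policy comparison, with the recorded added treatment shown by arm.
3. Sustained control without added treatment, in all randomised children, is a sensitivity analysis. It replaces any between-arm comparison of recurrence among responders, which becomes descriptive only.
4. The sponsor reconciles the open treatment choice after week 12 with the rule on non-permitted drugs and states which applies in follow-up.

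Cost: a little programming by the existing third party, with no change to any child's care. Trial status places the study at the statistical stage, and treatment decisions and relapses were to be recorded. The downside is that claims about follow-up become more modest.

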Tanshinone IIA is the main component of danshen (*Salvia miltiorrhiza*). Two studies [14, 15] reported that the therapeutic effects were better in a group treated with tanshinone IIA sulfonic acid sodium injection (TIIa) combined with GC than in the group treated with GC alone. Two other studies [16, 17] also found that TIIa combined with TG produced a higher level of decline in D-dimer and fibrinogen (FIB), and a longer prothrombin time (PT) at 4 weeks and 12 weeks than were observed in a TG group.

Qingrezhixue granule is a type of hospital preparation based on related TCM therapy that was first proposed by [name] and is made by the Affiliated Hospital of Henan University of TCM (Patent No. 2018 1011 8156.8). Each packet of granules contains the following drugs: Dihuang (*Rehmanniae radix*), Mudanpi (Cortex Moutan), danshen (*S. miltiorrhiza*), hanliancao (*Eclipta alba*), Chishao (*Radix paeoniae* Rubra), Sanqi (*Panax notoginseng*), xiaoji (*Herba cirsii*), and qiancao (Radix Rubiae). Unlike modern medicine, TCM is based on syndrome differentiation and is determined according to clinical manifestations and physical conditions. For example, the [name] “primary syndrome” and “secondary syndrome” system classifies five TCM patterns of syndromes: wind heat complicated with blood stasis, blood heat complicated with blood stasis, dampness heat complicated with blood stasis, yin deficiency complicated with blood stasis, and both qi and yin complicated with blood stasis [18]. Qingrezhixue granules play a key role in clearing heat and cooling blood, thereby promoting blood circulation and removing blood stasis. Other herbs can also be added if necessary according to the type of syndrome.

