### Blinding

Because TCM syndrome differentiation is needed during the research process, this is an open-label trial. To improve patient compliance in patients who come to the Chinese Medicine Hospital for TCM treatment, a regular group will be treated with Chinese medicine granule simulation drugs (placebo).

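### Clinicians who know the arm decide clinical control and relapse in follow-up, although control is a set of recorded laboratory limits that could be applied without knowledge of the arm

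*Protocol article*

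**What the plan says.** **Who decides.** In the protocol article, Intervention, follow-up stage (weeks 12-48), the clinicians who evaluate the follow-up laboratory results are described as "determining whether there is a relapse or whether the patient has reached clinical control standards) are not blinded" to the child's assignment.

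**What control means.** The same section sets the standard as "RBC counts and 24-h protein in urine are at normal levels, and urine routine examinations are negative for protein and occult blood". Table 4 repeats it as a category of response, for example "24-h urinary protein quantity is normal", together with RBC at or below 5/HP and negative dipstick results.

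**What depends on it.**
- The Statistical analysis section states: "Logistic regression is used to show a difference in the prevalence of clinical control/remission in both groups".
- The sample size rests on week-4 control rates for proteinuria of 48.6% and 35.7%.
- A main aim of follow-up is to "determine the disease recurrence rate".
- For children not controlled at week 12, "other treatment options could be appropriately selected in the professional judgment of the clinicians".

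**Why the trial is open.** The Blinding section gives one reason: "Because TCM syndrome differentiation is needed during the research process, this is an open-label trial".

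**Relapse.** The article says that a relapse is to be recorded and treated, but gives no laboratory criterion for it.

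**The concern.** An open-label treatment phase does not require open-label classification of outcomes. Where an outcome is a fixed function of recorded laboratory values, the step from values to category can be taken without the arm label. Here the article assigns that step in follow-up to people who know the arm.

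Borderline children are the ones at risk: a trace dipstick reading, an RBC count close to 5/HP, or a rise that may be transient. If these are resolved more favourably in one arm, the comparison of control rates shifts with no treatment effect. Recurrence is more exposed than control, because without a stated criterion the event is what the treating clinician records. The call on control also opens discretionary treatment after week 12, so a difference in calls can carry over into later results.

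**Working it through.** **1. The text side by side**

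| Element | What the article provides | Needs knowledge of the arm? |
|---|---|---|
| Measured 24-h protein (Outcomes) | laboratory quantity at 17 time points | no; no clinician assigns it |
| Clinical control (Intervention, Table 4) | laboratory limits only | no; a program can apply them |
| Recurrence (Intervention) | no criterion stated | no, once a criterion is fixed |
| Syndrome differentiation (Blinding) | guides herbal treatment | yes, for treatment only |

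The raw material for a programmed derivation exists. Laboratory reports are source data (Data collection and management), and each centre's normal reference values are to be attached (Quality control). The third party is named for the statistical analyses. It is not said to classify outcomes without the arm label.

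**2. Group sizes, from the plan's own figure**

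Control 35.7%, TCM 35.7% + 15 points = 50.7%, ratio 2:1, power 90%, one-sided α = 0.05, unpooled variance:

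n(control) = (1.645 + 1.282)² × [0.357 × 0.643 + (0.507 × 0.493)/2] / 0.15² ≈ 135, so the total is 3 × 135 = 405, as stated.

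The article does not state sidedness; a two-sided test gives 498 by the same formula. That is a separate matter. The sizes used below are 270:135 (the 405) and 333:167 (the 500).

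**3. Illustration of size**

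Assumptions, none of them from the article:
- no true effect;
- true control p = 0.357 in both arms (the article's week-4 comparator rate for proteinuria);
- a fraction f of uncontrolled TCM children is called controlled;
- no misclassification in the control arm;
- two-sided 5% test.

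Apparent TCM rate: p_T = p + f(1 − p). False difference: d = f × 0.643.

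Rejection probability = Φ[(d − 1.96·SE0)/SE1] + Φ[(−d − 1.96·SE0)/SE1], with SE0 pooled and SE1 unpooled.

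Worked case, f = 0.05 at 270:135:
- p_T = 0.357 + 0.05 × 0.643 = 0.389; d = 0.032
- pooled rate = (0.357 + 2 × 0.389)/3 = 0.378
- SE0 = √[0.378 × 0.622 × (1/135 + 1/270)] = 0.0511
- SE1 = √[0.357 × 0.643/135 + 0.389 × 0.611/270] = 0.0508
- Φ(−1.34) + Φ(−2.61) = 0.090 + 0.005 = 0.095

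| Assumed f | False difference (points) | Type I error, 270:135 | Type I error, 333:167 |
|---|---|---|---|
| 0% | 0 | 5.0% | 5.0% |
| 2% | 1.3 | 5.7% | 5.9% |
| 5% | 3.2 | 9.5% | 10.6% |
| 10% | 6.4 | 23.5% | 28.0% |

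If true control is 60%, fewer children can be misclassified. At f = 5% (0.05 × 0.40 = 2.0 points) the error is 6.8% or 7.2%; at f = 10% (4.0 points) it is 12.5% or 14.2%.

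**The case against.** **The primary indicator is a measurement.** The Outcomes section names 24-h urinary protein quantity, and no clinician assigns that number. A reader might infer that the primary outcome as a whole is biased; the text does not support this. Some exposure remains, because Table 4 puts its response categories under a primary-outcome heading and control drives the sample size.

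**The link to the analysis is not stated.** A reader might infer that the logistic model uses the clinicians' calls. The article does not say so. The sentence on blinding stands beside rules on stopping or changing treatment, where knowing the arm is normal, and derivation rules may be in a full protocol or SAP that is not shown. This lowers certainty about the efficacy categories. It does not remove the point, since the only assessors the article names for control and relapse in follow-up are the unblinded clinicians.

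**Checks exist.** It would be wrong to say the plan has none. It provides laboratory source reports, double data entry, queries, a data audit, three-grade quality control and an independent DMC. These could catch a child called controlled against an abnormal recorded value. They are not blinding, and for relapse they have no stated criterion to check against.

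**The assessors' interest.** The granules are "made by the Affiliated Hospital of Henan University of TCM", and the Study setting section names the First Affiliated Hospital as sponsor and recruiting site. A reader might infer that some assessors work for the patent owner. The article gives a patent number but no holder, so this cannot be claimed. Five collaborating hospitals also recruit.

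**The error rates are assumed.** They run in one direction and in one arm, and at 2% the effect is slight. The 35.7% is a treatment-stage rate for proteinuria, not the full composite in follow-up. All of this stands, and the figures show sensitivity only.

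**Conclusion.** The point holds in a limited form. In follow-up the article gives the determination of control and relapse to clinicians who know the arm, and nothing in its stated reason for the open label requires this. Disclosing it does not remove the bias. The exposure is greatest for the recurrence rate, smaller for the control and efficacy categories, and slight for measured 24-h protein.

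The size cannot be known from the article. Under the assumptions shown, two-sided type I error for the control comparison goes from 5% to about 6% (2% misclassified), 10% (5%) or 24-28% (10%), and rises less if the true control rate is higher. No such figure can be given for recurrence, because it has no stated definition. The sentence on blinding covers follow-up results; for earlier visits the trial is open-label and no blinded assessor is described. This should be fixed before the comparison is made, but it is no ground for setting aside the measured protein results.

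**What to change.** **Change.**
1. State that for all analyses the third-party analysis centre derives clinical control by program from the recorded laboratory values and each centre's reference limits, with arms coded.
2. Derive recurrence in the same way. Fix its analysis definition from those values before the arms are uncoded.
3. Add a sensitivity analysis that counts a recurrence only if the abnormality is confirmed at the next scheduled visit. Counting any single later failure of a limit would turn every transient rise into an event.
4. Keep the clinicians' calls for patient care only, and report by arm how often they disagree with the derived outcome. The definition is for analysis and changes no treatment rule.

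**Cost.** Analysis wording and one derivation program, with no extra visits, tests or staff and no change to the sample size. The Trial status section places the trial at the data-analysis stage. Blinded assessment visits can no longer be added, but derivation from recorded values is still feasible. If the arms have already been uncoded, the report should say so.

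**What it leaves.** Some children's derived outcome will differ from the clinician's entry. Bias in the reading of samples, or from discretionary treatment after week 12, is not removed.
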